#### RT group

The RT group will undertake three training sessions per week for 12 weeks. Each session will take approximately 30 min. Each training session will be supervised by an exercise specialist to ensure that each exercise is performed using the correct method. Both lower limbs will be trained using the following exercises: knee extension, knee flexion, ankle plantarflexion, ankle dorsiflexion, extended leg raises, hip abduction, hip adduction, and hip extension. The exercise regimen will comprise three sets of 10 repetitions for each of these exercises. Each set will be performed bilaterally, starting with the less affected limb. These exercises, which have been widely used in previous studies [29, 30], will be selected primarily to strengthen the muscles directly supporting the knee. Thera-Band® resistance bands (The Hygenic Corporation, Akron, OH, USA) will be used during the RT. For participants who cannot perform 10 repetitions with the lightest resistance band for a given exercise at the baseline, the maximum number of repetitions that can be completed satisfactorily will be prescribed with an initial goal of progressing to 10 repetitions maximum. Otherwise, RT exercises will be progressed by adding a greater stretch to the prescribed band to provide greater resistance or by moving up to the next strength of resistance band.

#### Control group

The control group will attend one 60-min group session per week. The session will consist of a 30-min lecture, followed by a 30-min discussion. The control group will receive 12 weeks of health education. The lectures will cover health-related topics, such as OA, aging, and nutrition. The participants in the control group will be asked to maintain their previous lifestyle and not to take part in any other regular rehabilitation programs.

### Outcome measures

All outcome measure assessments will be performed by the main and blinded research assistant at the baseline, 3 months (after intervention), and 6 months (follow-up). A demographic questionnaire will be completed before the intervention. Demographic information includes participant characteristics (i.e., sex, age, Body Mass Index, affected side, Lequesne Knee Score, and current drug treatment). Each test will be conducted by the same assessor.

#### Primary outcome measures

##### Anthropometric measurements

The body weight and height of each participant in minimal clothing and bare feet will be measured. Body height will be measured to the nearest 0.5 cm with a fixed stadiometer (Holtain Ltd., Crymych, Dyfed, UK). Body weight will be measured to the nearest 0.1 kg on a standard scale (TBF 543 model; Tanita, Tokyo, Japan). Body Mass Index will be calculated as follows:$$ \mathrm{Body}\  \mathrm{mass}\  \mathrm{in}\mathrm{dex}\kern0.5em =\kern0.5em \mathrm{Body}\  \mathrm{weight}\  \mathrm{in}\ \mathrm{kg}/{\left(\mathrm{Body}\  \mathrm{height}\  \mathrm{in}\ \mathrm{m}\right)}^2. $$

##### Gait analysis during walking and stair climbing

Kinematics and kinetics data will be collected and analyzed using a Vicon Motion Analysis System (Vicon MX-13, Oxford Metrics, Oxford, UK) with nine infrared cameras that record three-dimensional motion at 200 Hz and coupled with force plates (models 9286AA, Kistler Instruments Corp., Winterthur, Switzerland) that record ground reaction force at 1000 Hz. The trajectories of 45 retroreflective markers (14 mm in diameter) will be captured at different landmarks of the participant according to a plug-in gait marker set.

These biomechanical data will be collected while each participant performs three tasks:Level walking at preferred speed and faster speedStair climbing

The experimental staircase consists of six steps. The step dimensions are 17.8 cm (height), 91.5 cm (wide) and 28.0 cm (tread) with a handrail [31]. Three force platforms (9286AA, Kistler Instruments Corp., Winterthur, Switzerland) will be embedded in the second, third, and fourth steps of the staircase. The participants will be asked to walk, ascend, and descend at their natural speed without any reference to the force platforms.

##### Knee extensors and flexors strength

Knee extensor and flexor strength of the affected knee joint will be measured using an isokinetic dynamometer (850, Biodex, Shirley, NY, USA). The assessor will secure the participants to the device at the upper chest, pelvis, and distal femur on the tested side with Velcro straps. Three maximum concentric contractions for the knee extensors and flexors will be performed at an angular velocity of 90°/s. All data will be normalized by kilogram of body weight. The highest peak torque will be used for analysis. The dynamic endurance of the knee extensors and flexors will be assessed by measuring 40 repeated maximum isokinetic contractions at an angular velocity of 180°/s. The work of each contraction in the knee moving angle of 80°–10° will be recorded. The Endurance Index is defined as the ratio of the work performed during the last five contractions over the first five contractions.

##### Proprioception test of the knee and ankle

This measurement method was reported in our previous studies [32]. Knee and ankle proprioception will be tested using an electrically driven movable frame. During the tests, the participant will sit on a chair with the dominant leg supported by the frame. The leg can be passively moved in a flexed or extended direction at a velocity of 0.4°/s. Once the participant is able to detect the leg motion, they will press a handheld “stop” button and confirm the direction of the motion. The rotation angles of the frame will be determined as the threshold for the detection of the knee and ankle joint. The mean values of the three trials in one direction will be used for the analysis.

##### Neuromuscular response

Neuromuscular response, indicated by muscle latency, will be assessed using electromyography (EMG) of the leg muscles while an unexpected perturbation is applied to the ankle. A customized trapdoor with an 18° tilt angle will be used to generate an ankle inversion perturbation while the participants stand barefoot on the trap doors. The Noraxon EMG system (Noraxon USA Inc., Scottsdale, AZ, USA) will be used to collect surface EMG signals from five muscles (rectus femoris, semitendinosus, gastrocnemius, peroneus longus, and anterior tibialis) of the right leg and onset signals at the trapdoor tilting with a sampling frequency of 1000 Hz. Both feet will be randomly tilted at least seven times to decrease anticipatory effects. The onset latency of the muscles refers to the time interval in milliseconds (ms) between the trapdoor initiation and the first rising front of the EMG burst from the baseline. The EMG onset will be visually determined by an experienced researcher.

Furthermore, muscle activation will be determined during level walking and stair climbing. EMG data will be collected from eight lower extremity muscles in accordance with the recommended muscles for gait analysis from Winter and Yack [33]; these muscles are the ipsilateral and contralateral erector spinae at the level of the iliac crest, rectus femoris, vastus medialis, vastus medialis, tibialis anterior, biceps femoris, peroneus longus, and gastrocnemius. The Noraxon EMG system (Noraxon USA Inc., Scottsdale, AZ, USA) will be used to collect surface EMG signals from these muscles of the right leg with a sampling frequency of 1000 Hz. The EMG signals from five complete gait cycles per task will be used in data reduction. Prior to the EMG data collection, maximal isometric contraction data will be gathered for each muscle. The mean EMG amplitude and on-off muscle timing during a gait cycle will be used in the data analysis [34].

#### Secondary outcome measures

##### Self-reported pain and physical functional capacity

A 10-cm Visual Analog Scale (VAS; 0, no pain; 10, maximal pain) will be used to assess self-reported pain related to knee joint movement.

The Western Ontario and McMaster Universities Osteoarthritis Index (WOMAC), a validated [35] and widely used OA-specific, self-reported questionnaire that assesses pain, stiffness, and function in patients with OA of the knee will be used to assess the symptoms and function of the participants. The WOMAC includes three subscales (pain, stiffness, and physical function) and 24 questions. Each question is scored from 0 to 4, with 0 indicating no pain and 4 indicating great pain.

The 36-item Short Form Health Survey (SF-36), which is a large-scale measurement tool used in evaluating the positive and negative aspects of the overall health status, will be used to indicate the overall health status of the participants. The parameter scores range from 0 and 100, and higher values indicate better health status [36]. This tool is easy to use, acceptable to patients, and fulfills the stringent criteria of reliability and validity [37].

The Beck Depression Inventory, a common scale used to assess the severity of depression of individuals, will be used to determine whether the WBV exercise and control group programs have different psychological effects on the participants [38]. Higher scores indicate high levels of depression. The achievement of more functional benefits with the WBV training program than with the control group programs might have psychological reflections.

##### Physical performance measures

The Berg Balance Scale is a widely used clinical test of the static and dynamic balance abilities of a person, and it comprises a set of 14 simple, balance-related tasks, ranging from standing up from a sitting position to standing on one foot. The total score ranges from 0 to 56, with 0–20 corresponding to a high fall risk, 21–40 a medium fall risk, and 41–56 a low fall risk [39].

The Timed Up and Go test (TUG), a reliable and valid measure of balance and mobility in patients with KOA [40], will be used to assess functional performance. Participants will be asked to stand up from a seat, walk 3 m, turn around, walk back, and sit down again. The test will be performed twice, and the faster time will be recorded. The entire walking test will be timed using a chronograph (in seconds).

The 6-minute Walk Distance test (6MWD), which is a simple method to indicate functional performance reliably and is frequently used in OA-related trials, will be used to measure the walking function of the participants. The distance walked in 6 min will be recorded in meters [41].

### Statistical analysis

SPSS for Windows, version 17.0 (SPSS Inc., Chicago, IL, USA) will be used for statistical analysis. If any participant withdraws from the trial, the missing values will be replaced by the last assessment score of the participant. And all available data will be analyzed using an intention-to-treat analysis. Chi-squared tests will be used to test for demographic differences among the WBV training, RT, and control groups.

An intention-to-treat analysis will be performed by including all participants in the analysis according to the original group allocation. The follow-up will be maximized regardless of the program attendance. Repeated-measurement analysis of variance will be used to evaluate for between- and within-group difference. Bonferroni’s post hoc test will used for comparing the results. Data will be presented as the mean and standard deviation, and significance will be set at 0.05.

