## Methods/design

### Study design

The study design is a prospective, single-blind randomized controlled trial. Three intervention programs, namely, a WBV exercise program, lower extremity RT, and a health education program, will be included in the study (Fig. 1). This study will be conducted at the Sport Medicine and Rehabilitation Center, Shanghai University of Sport. The power analysis with settings at *α* = 0.05, power (1 − *β*) = 0.80 and effect size = 0.25 showed that three groups of 120 participants in total was the required sample size. Given the dropouts, we decided to recruit 180 participants for the research. A total of 180 patients from community centers in Yangpu District, Shanghai, China will be included through advertisements placed in various community centers by the recruiter. A multidisciplinary team composed of clinicians, physiotherapists, and exercise specialists will run the program.

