**Fig. 1 Fig1:**
[figure not shown]
Flow diagram of study design

Prior to the initiation of the study, all participants will fill out the questionnaire with their details, including medical history and past and present job status. Participants will also complete the Mini-Mental State Examination and the Activities of Daily Living test, and will describe their exercise habits (frequency and duration). Informed consent will be requested from each participant prior to the inclusion in the study.

Participants who meet all study inclusion criteria and consent to participate will be randomly allocated to the WBV exercise, lower extremity RT, and health education groups via using computer-generated randomization by a research designer. The study nurse will assign participants to the interventions. Only the research designer and trainers will know the randomized assignments. The assessors will be unaware of the randomization and will not be involved in the exercise interventions. This study will include assessments at the following time points: before intervention, after 3 months of intervention, and after 3 months of further follow-up with no active intervention. The total study period will be 6 months. Additional files 1 and 2 represent SPIRIT Checklist, and schedule of enrollment, interventions and assessments﻿.

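### Last observation carried forward, the only missing-data rule in the article, biases the 3- and 6-month comparisons even under random dropout, with a net direction that depends on who drops out and when

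*Protocol article*

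**What the plan says.** The Statistical analysis section of the protocol article gives one rule for missing values. It begins "If any participant withdraws from the trial" and continues: "the missing values will be replaced by the last assessment score of the participant". This is last observation carried forward (LOCF), and no outcome is exempted. The same section states that "An intention-to-treat analysis will be performed by including all participants in the analysis according to the original group allocation" and that "Repeated-measurement analysis of variance will be used to evaluate for between- and within-group difference", with Bonferroni post hoc comparisons, and "significance will be set at 0.05". It names no other imputation, likelihood-based method or sensitivity analysis. It does add that follow-up will be pursued whether or not people attend their programme.

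The Study design and Outcome measures sections fix three assessments: baseline, 3 months at the end of the intervention, and a last one "after 3 months of further follow-up with no active intervention". On sample size, Study design gives power of "0.80 and effect size = 0.25 showed that three groups of 120 participants in total was the required sample size", and then: "Given the dropouts, we decided to recruit 180 participants for the research". No dropout rate is stated. The withdrawal criteria include an adverse reaction to either exercise programme, a reason that cannot arise in the education arm.

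**The concern.** With three visits, LOCF has only two values to carry, and each makes a strong assumption.

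- A participant lost before 3 months receives the untreated baseline score at 3 and 6 months, that is, zero change.
- A participant lost after 3 months receives the end-of-treatment score at the off-treatment visit. For that participant the rule assumes the answer to the question the visit is meant to settle. The Discussion lists this untreated follow-up period among the trial's strengths.

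The copied scores are then analysed as if they had been measured. At stake are the size of the 3-month effect and any claim about how long it lasts. Because the article fixes the rule, this is not a detail left open for an analysis plan that is not shown.

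**Working it through.** **The plan's own figures.** With three groups, α = 0.05, power 0.80 and effect size 0.25 read as Cohen's f (an assumption), a plain one-way ANOVA needs 159; at 120 its power is 0.68. The stated 120 is reproduced by the between-groups test of a repeated-measures ANOVA with m = 2 measurements and correlation ρ = 0.5, neither of which is stated:

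λ = N·m·f² / (1 + (m − 1)ρ) = 120 × 2 × 0.0625 / 1.5 = 10, power 0.805.

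Recruiting 180 to keep 120 implies an allowance of 1 − 120/180 = 33.3%. This is an inferred margin, not a forecast.

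**Expected LOCF effect.** Let e be the fraction lost before 3 months and l the fraction lost between 3 and 6 months, random and equal across arms. Let δ₃ and δ₆ be the true effects.

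- 3 months: (1 − e)·δ₃
- 6 months: (1 − e − l)·δ₆ + l·δ₃ + e·0

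These expectations follow from the filling-in rule, whatever test is applied afterwards.

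**Numbers.** The documents give no effect in SD units, dropout timing or correlation. Assumed here: δ₃ = 0.60 SD, 60 per arm (equal allocation), correlation 0.6 between visits. Coverage and rejection come from simulating a two-arm ANCOVA on LOCF-filled data, 4,000 trials per scenario.

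| Loss pattern | Quantity | True | LOCF | Simulated |
|---|---|---|---|---|
| 1/3 before 3 months | 3-month | 0.60 | 2/3 × 0.60 = 0.40 | coverage about 65% |
| 20% before 3 months | 3-month | 0.60 | 0.8 × 0.60 = 0.48 | coverage about 86% |
| 10% before 3 months | 3-month | 0.60 | 0.9 × 0.60 = 0.54 | coverage about 94% |
| 1/3 after 3 months | 6-month | 0 | 1/3 × 0.60 = 0.20 | rejection about 26% |
| 20% after 3 months | 6-month | 0 | 0.2 × 0.60 = 0.12 | rejection about 12% |
| 10% after 3 months | 6-month | 0 | 0.1 × 0.60 = 0.06 | rejection about 6% |
| 1/6 before, 1/6 after | 6-month | 0 | 1/6 × 0.60 = 0.10 | rejection about 11% |
| 1/6 before, 1/6 after | 6-month | 0.30 | 0.20 + 0.10 = 0.30 | coverage about 95% |
| 1/6 before, 1/6 after | 6-month | 0.60 | 0.40 + 0.10 = 0.50 | understated |

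With one third lost before 3 months, ANCOVA on the observed values alone gives 0.60 SD, about 95% coverage and power 0.90. LOCF gives power 0.87.

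**Unequal dropout.** Suppose WBV improves by 0.5 SD with 10% lost before 3 months, and control improves by 0.3 SD with 33% lost. LOCF gives 0.9 × 0.5 − 0.67 × 0.3 = 0.45 − 0.20 = 0.25, against a true 0.20. Here the 3-month effect is inflated.

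**Precision.** With one third lost early, 40 per arm are observed and the ANCOVA standard error is √(2/40) × √(1 − 0.6²) = 0.224 × 0.8 = 0.179. Complete data on 60 per arm would give √(2/60) × 0.8 = 0.146. LOCF reports about 0.129, less than even complete data would give. Yet 0.129 matches the LOCF estimator's own spread of 0.130, so the interval is the right width around the wrong target. The bias alone explains the coverage: 0.20/0.129 = 1.55, and Φ(1.96 − 1.55) ≈ 0.66.

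**The case against.** A reader might infer three stronger things that the documents do not support.

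- *That the direction is predictable: dilution at 3 months, apparent maintenance at 6.* The unequal-dropout example inflates the 3-month effect. At 6 months early and late losses oppose each other: an even split leaves a true 0.30 unbiased and understates a true 0.60. The article gives neither the timing of dropout nor its balance between arms.
- *That intervals are too narrow and therefore under-cover.* LOCF does claim more information than was collected, but the coverage loss comes mainly from bias. With no true effect and one third lost early, rejection stays near 5%.
- *That one third will be lost.* The rate is inferred from the recruitment margin. The one-third rows that place all loss in one window are worst cases, and both cannot occur in the same trial within an allowance of 60.

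Two further points are fair. Pursuing follow-up regardless of attendance separates stopping the programme from missing an assessment, and should reduce the amount imputed; with 5% lost in each window, the 3-month estimate is 0.57 for a true 0.60 with nominal coverage. The simulated test is also not the planned three-group ANOVA with Bonferroni, so the coverage and rejection rates are illustrative.

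These points limit the size and sign of the bias. They do not rescue the rule: better follow-up reduces missing data but supplies no other way to handle what remains, and a bias that can go either way cannot be defended as conservative. An analysis plan not shown could add sensitivity analyses, but the article's stated handling would still be LOCF.

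**Conclusion.** The concern holds in this form: LOCF, as the only stated rule, biases the between-group comparisons even when dropout is completely random. With equal early dropout d the 3-month effect shrinks by the factor (1 − d). With unequal dropout and change in all arms it can move either way. The net bias at 6 months depends on when participants are lost and on the true 6-month effect.

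Under the stated assumptions the size runs from little harm at about 10% loss to the worst cases at one third. The bias formulas assume that participants who leave would otherwise have shared their arm's effect. Withdrawal for adverse reactions, possible only in the exercise arms, could make losses both unequal and informative, so the random-dropout figures are not an upper bound.

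**What to change.** Replace the LOCF sentence with:

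> Outcomes will be analysed as randomised with a likelihood-based linear mixed model for repeated measures (group, visit, group-by-visit, unstructured covariance), with baseline, 3-month and 6-month values all modelled as outcomes and baseline means constrained equal across groups, using all observed data without single imputation.

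Modelling baseline as an outcome matters: if it were a covariate, participants with no post-baseline value would drop out of the model, contrary to the stated intention-to-treat set.

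The model assumes data missing at random, so add one sensitivity analysis for departures from that. Use multiple imputation with either a pre-specified range of delta shifts or a reference-based rule, and name which; they are different methods.

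The cost is wording and slightly more analysis work. The SPSS package already named can fit mixed models, and data collection does not change. The Trial status section says that recruitment is ongoing, so the change can be made and dated before analysis.

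### Chi-squared is the only test named for baseline demographics, but three of the six listed (age, BMI, Lequesne score) are numeric

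*Protocol article*

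**What the plan says.** Under Statistical analysis, the protocol article says: "Chi-squared tests will be used to test for demographic differences among the WBV training, RT, and control groups". No second test is given for baseline variables, and no grouping of numeric variables is described. Under Outcome measures, the demographic set is defined as "sex, age, Body Mass Index, affected side, Lequesne Knee Score, and current drug treatment".

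BMI comes from fine measurements. Under Anthropometric measurements, "Body weight will be measured to the nearest 0.1 kg on a standard scale" and "Body height will be measured to the nearest 0.5 cm with a fixed stadiometer". The Inclusion criteria limit age to 50–70 years and the Lequesne score to 1–7.

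The Statistical analysis section also says that data will be shown as mean and standard deviation, that "significance will be set at 0.05", and that treatment effects will be assessed by repeated-measures ANOVA with Bonferroni post hoc tests.

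**The concern.** A Pearson chi-squared test compares the distribution of unordered categories. It suits sex, affected side and drug treatment. Applied to a numeric variable as recorded, it treats each distinct value as a separate category and ignores the order. When nearly every participant has a different value, the table has about as many categories as participants and carries almost no information about the arms.

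At stake is the baseline table. A line reporting no significant difference in BMI could be a product of the test and not of the data, and readers could take it as evidence that the arms were alike. BMI is also described under the primary outcome measures, so it is not an incidental variable here.

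**Working it through.** **Plan's own figure.** The article gives no figure for the baseline tests. Its only related number is the sample size: 120 required and 180 recruited (Study design). The 120 can be reproduced for the between-group effect of a repeated-measures ANOVA with effect size 0.25, two measurements and a correlation of 0.5 (power 0.805; the last two inputs are assumptions). The baseline tests play no part in it.

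**Inputs.** N = 180 in three arms (Study design). The allocation ratio is not stated, so 60 per arm is assumed. Age 50–70 gives 21 values if recorded in whole years. Weight is recorded to 0.1 kg and height to 0.5 cm. Simulated means, SDs and cut-points are assumptions: age SD 5 years, BMI SD 3.5 kg/m², Lequesne SD 1.6 in whole numbers.

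**1. Raw BMI, all values distinct.** Each of the 180 categories holds one participant, with an expected count of 1/3 in each arm. One category contributes

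(1 − 1/3)²/(1/3) + 2 × (1/3)²/(1/3) = 4/3 + 2/3 = 2.

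The total is 180 × 2 = 360 on (180 − 1) × (3 − 1) = 358 degrees of freedom, p = 0.460. The values themselves do not enter the calculation, so a 5 kg/m² shift in one arm leaves p unchanged. Equal arms are not needed. If arm j holds a share p_j, each of its members contributes 1/p_j − 1, and the sum 180 × Σ p_j(1/p_j − 1) = 180 × (3 − 1) is again 360.

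**2. BMI at the stated precision.** With weight to 0.1 kg and height to 0.5 cm, about 179 of 180 simulated BMI values are distinct. With one arm shifted by 0.53 SD, chi-squared rejected in 0 of 500 trials and ANOVA in 83%.

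**3. Age, Lequesne score and grouped values.** The table gives rejection rates at 0.05 in 3,000 simulated trials, with arm means at −0.306, 0 and +0.306 SD. This is f = 0.306 × √(2/3) ≈ 0.25.

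| Variable, as tested | Chi-squared, no difference | Chi-squared, f ≈ 0.25 | ANOVA or Kruskal–Wallis, f ≈ 0.25 |
|---|---|---|---|
| BMI to 1 decimal | 0.001 | 0.005 | 0.85 |
| BMI in 3 bands | 0.049 | 0.63 | 0.85 |
| Age in whole years | 0.032 | 0.24 | 0.84 |
| Age in 4 bands | 0.052 | 0.62 | 0.84 |
| Lequesne, whole numbers | 0.047 | 0.49 | 0.83 |

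The last column uses the ungrouped variable. A second age simulation (2,000 trials, one arm shifted by 0.53 SD, so f = 0.53 × √2/3 ≈ 0.25) gave 0.22 against 0.84. For whole-year age the table has 21 × 3 = 63 cells and a mean expected count of 180/63 = 2.9, which fits the slightly low rejection rate of 0.032.

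**The case against.** **Wording.** The article does not say that every demographic is tested this way, nor that numeric variables are tested ungrouped. Chi-squared is right for three of the six. A condensed article may leave the coding of baseline variables to a fuller document. This stands, and it rules out a reading that a reader might infer: that all the planned baseline p-values are meaningless. The table shows otherwise. Age and Lequesne score respond to a shift, and grouped variables hold their level. Only near-unique raw values such as BMI give an uninformative result. The objection does not remove the point, because the article is not silent: it names one test for a set of variables that it defines itself.

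**Consequence.** After sound randomisation any baseline difference is due to chance, so these p-values decide little whichever test is used. The imbalances simulated above are also rare. With 60 per arm, one arm against the other two has a standard error of √(1/60 + 1/120) = 0.158 SD. A shift of 0.53 SD is then 0.53/0.158 ≈ 3.4 standard errors (two-sided p about 0.0008). If the mean and SD are shown for baseline variables, as the article's general statement suggests, readers can see an imbalance directly. All of this stands and keeps the point small. A reader might also infer that the treatment comparison is biased. The documents do not support that: no outcome analysis, choice of covariate or sample size depends on the baseline tests.

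**Conclusion.** The point holds in a limited form, and its severity is minor. The only test named for demographic differences does not suit age, BMI and Lequesne score.

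- **Raw BMI:** the p-value is about 0.46 whatever the data show. This is exact if all 180 values differ and close to it at the stated measurement precision.
- **Age, Lequesne score or grouped values:** the test does not reject too often but loses power, to between about 0.22 and 0.63 where ANOVA or Kruskal–Wallis would have 0.83 to 0.85. These rates rest on 60 per arm and on the assumed SDs and cut-points.

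The damage is confined to how baseline comparability is reported.

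**What to change.** Replace the chi-squared sentence in the Statistical analysis section. Either limit chi-squared to sex, affected side and current drug treatment, or drop baseline p-values altogether. Describe age, BMI and Lequesne score by mean (SD) and the categorical variables by counts and percentages. If a test is kept for the numeric variables, use one-way ANOVA or Kruskal–Wallis. The cost is one or two sentences, with no new data or participants and no change to the sample size.

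Separately, precision can be gained at no cost in data by comparing the arms on the 3- and 6-month values with each outcome's baseline value as a covariate, whatever imbalance is seen. Baseline would then no longer be a level of the repeated-measures factor, so the main model must be restated before the data are analysed. This does not cure imbalance in age, BMI or Lequesne score, and the correction above does not depend on it.

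### The only between-group test named is that of a repeated-measures ANOVA with baseline as one of its visits; a baseline-adjusted contrast at a stated visit should be named instead

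*Protocol article*

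**What the plan says.** The efficacy analysis in the Statistical analysis section of the protocol article is two sentences. The first reads "Repeated-measurement analysis of variance will be used to evaluate for between- and within-group difference". The second adds that Bonferroni's "post hoc test will used for comparing the results", without saying which results. The level is fixed by "significance will be set at 0.05". The Study design section gives the assessments as "before intervention, after 3 months of intervention, and after 3 months of further follow-up with no active intervention", and the Outcome measures section repeats the three time points without ranking them. The Background states the aim as the efficacy of a 12-week WBV programme compared with RT and with health education. For sample size, the Study design section says "effect size = 0.25 showed that three groups of 120 participants in total was the required sample size", and then "Given the dropouts, we decided to recruit 180 participants for the research".

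**The concern.** A repeated-measures ANOVA of three groups over three visits yields a group effect, a time effect and their interaction. The wording points to the first two and is silent on the third.

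- **Between-group effect.** It compares group means averaged over all visits. One of the three is baseline, where randomisation makes the expected difference zero. Another is the 6-month visit, after three months without intervention, when some of the effect may have faded.
- **Within-group effect.** This is change over time. It is not a comparison of treatments.
- **Group by time.** This term carries the treatment signal. It is an omnibus test on 4 degrees of freedom and does not say which groups differ or when, whereas the aim is two specific comparisons.

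In none of these is baseline used as a covariate. At stake is a real WBV effect missed through dilution, or an improvement within the WBV arm read as efficacy.

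**Working it through.** **The plan's own figure.** Read the effect size 0.25 as Cohen's f (the article does not name the metric), with three groups, alpha 0.05 and power 0.80.

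- One-way ANOVA, λ = f²N: at N = 120, λ = 0.0625 × 120 = 7.5 and power is 0.68; the required N is 159.
- Between-group main effect over m visits with correlation ρ, λ = f²Nm/(1 + (m − 1)ρ): with m = 2 and ρ = 0.5, λ = 7.5 × 2/1.5 = 10, power 0.805, required N exactly 120. With m = 3, N is 108 at ρ = 0.5 and 117 at ρ = 0.6.
- Group-by-time interaction, λ = f²Nm/(1 − ρ), at ρ = 0.5: N = 42 (m = 2) or 36 (m = 3).

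Of these, 120 is matched only by the visit-averaged group effect. Because m and ρ are assumed, this is circumstantial evidence of what the planners had in mind.

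**Dilution.** Let the difference be 0 at baseline, δ at 3 months and rδ at 6 months. The averaged difference is δ(1 + r)/3, which is 0.67δ for r = 1 and 0.50δ for r = 0.5.

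**Pairwise power.** Assumptions that are not in the article: δ = 0.60 SD, ρ = 0.6 between any two visits, equal variances, equal allocation (180/3 = 60 per arm). Alpha is 0.05/3 for three pairwise tests, with 177 residual degrees of freedom (critical t about 2.42). Noncentrality is the standardised effect × √(60/2) = effect × 5.477.

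| Comparison | Standardised effect | Noncentrality | Power |
|---|---|---|---|
| Averaged over visits, r = 1 | 0.40/√(2.2/3) = 0.467 | 2.56 | 56% |
| Averaged over visits, r = 0.5 | 0.30/√(2.2/3) = 0.350 | 1.92 | 31% |
| 3 months, unadjusted | 0.60 | 3.29 | 81% |
| Change, baseline to 3 months | 0.60/√(2 × 0.4) = 0.671 | 3.67 | 89% |
| 3 months, baseline-adjusted | 0.60/√(1 − 0.36) = 0.750 | 4.11 | 95% |

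The sample-size ratio of the averaged to the adjusted comparison is (0.750/0.467)² = 2.6 for r = 1 and (0.750/0.350)² = 4.6 for r = 0.5. With 40 per arm (120/3) the five powers are about 37%, 20%, 60%, 71% and 82%.

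**Interaction test.** Place RT halfway between control and WBV. The centred group effects −0.30, 0, 0.30 have sum of squares 0.18. The centred visit profile (0, 1, r) has sum of squares 0.667 for r = 1 and 0.50 for r = 0.5. With λ = 60 × 0.18 × (visit sum of squares)/(1 − ρ), λ = 18.0 and 13.5. Power on 4 and 354 degrees of freedom at 0.05 is about 94% and 85%.

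**Sensitivity to ρ, 60 per arm.**

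| ρ | Averaged, r = 1 / 0.5 | Unadjusted 3 months | Change | Adjusted 3 months | N ratio, r = 1 / 0.5 |
|---|---|---|---|---|---|
| 0.3 | 72% / 44% | 81% | 64% | 85% | 1.3 / 2.3 |
| 0.6 | 56% / 31% | 81% | 89% | 95% | 2.6 / 4.6 |
| 0.7 | 51% / 28% | 81% | 96% | 98% | 3.5 / 6.3 |

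The adjusted contrast has the highest power among the pairwise comparisons in every row. Its margin over the unadjusted 3-month test grows with ρ, and its margin over change scores shrinks.

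**The case against.** A reader might infer that the plan compares means averaged over baseline, 3 and 6 months, and so needs 2.6 to 4.6 times as many patients as it should. The document does not support that. It never says that marginal means are the decisive comparison, that post hoc tests are run on them, or that the interaction will be ignored. The same ANOVA supplies a group-by-time test, which is valid in a randomised trial and, under these assumptions, has power not far below that of the adjusted contrast. Bonferroni comparisons can also be made visit by visit. The match of 120 to a main-effect calculation rests on an assumed number of visits and correlation.

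Two further points are fair. The article gives neither the correlation, the retention at 6 months nor a 0.60 SD target, and at ρ = 0.3 with full retention the ratio is only 1.3. Nor does it rank 3 months above 6; the Discussion counts the untreated follow-up as a strength. If the effect persists, adjusting the mean of the 3- and 6-month values does better still: 0.94 against 0.80 for 3 months alone, at N = 120, f = 0.25 and ρ = 0.5.

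It can also be said that the choice of contrast and covariates is commonly left to a SAP. That answers a complaint of silence. It does not fully answer this point, because the article does commit to a method and to the two differences it will evaluate, and those do not include the term that isolates the treatment effect.

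**Conclusion.** The point holds conditionally. The only between-group test named has baseline among its visits, and no interaction, visit or baseline adjustment is stated. If the main effect and post hoc tests on it are used, the loss is large: the effect is cut by one third to one half, and power is 56% or 31% against 95% under the stated assumptions. If the tests are run per visit or on change, the loss at ρ = 0.6 is moderate, about 14 or 6 points. The interaction is a sound omnibus test but leaves the two comparisons of interest unanswered. That averaging dilutes the effect is certain; that the investigators intend to average is not. The case for changing the wording does not depend on which reading is right, because the adjusted contrast had more power than each pairwise alternative for ρ from 0.3 to 0.7.

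**What to change.** Analyse the 3- and 6-month values as outcomes in a mixed model or ANCOVA, with the baseline value as covariate and terms for group, visit and group by visit. Base efficacy on the adjusted WBV-minus-control and WBV-minus-RT differences, each with a 95% confidence interval, at a visit that the investigators name in advance. Three months, the end of the 12-week programme, is the natural choice, but it is theirs to make. Apply Bonferroni or Holm over those named contrasts, and report within-group changes descriptively only.

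The cost is a few sentences in the analysis section or SAP. Baseline values are already scheduled for collection, and no extra patients or software are needed. The article reports recruitment as ongoing, so the change should be dated and fixed before any comparison by arm.
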